### Intervention

#### Overview

The intervention protocol includes an on-site awareness program on prehypertension and hypertension (Table 1) and an mHealth app. The information in the mHealth app is provided under the following headings in both English and Kannada: about blood pressure, prehypertension and hypertension, diet, exercises, yoga, smoking and alcohol consumption, and sleep. The information leaflet encompassing the details of teaching provided during the on-site awareness program will be given to the participants of all the clusters after the study at the end of sixth month.

**Table 1 table1:** Plan for the mHealth intervention. The total duration of teaching is 45 minutes.

Areas of teaching in the teaching plan	Duration (min)
Introduction	2
Meaning of prehypertension	2
Risk factors for prehypertension	5
Lifestyle modifications for the control of blood pressure	10
Significance of adherence to lifestyle practices in controlling blood pressure	5
Role of diet in reducing blood pressure focusing on DASH^a^ diet guidelines	5
Conclusion	1
Discussion	15

^a^DASH: dietary approach to stop hypertension.

#### mHealth App

The mHealth app designed for the study, INFOBP, was customized to the research topic and the population of interest. The app was designed with the support of the team from Information Technology. It provides information on prehypertension and its risk factors as well as lifestyle modifications, including the dietary approach to stop hypertension (DASH) diet and exercise, for preventing and managing the complications of prehypertension. The information provided in the app is available in both English and Kannada. When responding to questionnaires, the participants have the freedom to make changes to their responses until they submit the questionnaire. Once submitted, no changes can be made from the user’s end. The information provided in the app can be viewed by the participants any number of times at their own pace. The app’s user flow is depicted in Figure 3.

**Figure 3 figure3:**
[figure not shown]
User flow diagram for the mHealth app on prehypertension. HTN: hypertension.

A screenshot of the mHealth app is presented in Multimedia Appendix 2. To evaluate the validity and applicability of eHealth trials, the CONSORT-EHEALTH (Consolidated Standards of Reporting Trials of Electronic and Mobile Health Applications and Online Telehealth) checklist [29] was used and is provided in Multimedia Appendix 3. To check the quality and usefulness of the mHealth app, the mobile application rating scale (Multimedia Appendix 4) [30,31] was used by 12 participants from the experimental group after a few days of app usage. The participants’ responses are provided in Multimedia Appendix 5. Due permission was obtained from the original author for using the mobile application rating scale.

Both the control and intervention groups will receive education on prehypertension. The experimental group will also receive the mHealth app free of cost, provides information on prehypertension, risk factors for prehypertension, lifestyle modifications (including the DASH diet and exercise), and strategies for preventing hypertension and its complications. The mHealth app (INFOBP) will be installed on the mobile devices of all students in the intervention group, and they will receive orientation on its use. The experimental group will be monitored for adherence to lifestyle practices every 15 days through the mobile app, and reinforcement and reminder messages will be sent to nonresponders. All participants in the experimental group will receive a message of encouragement through the app every 15 days to continue practicing the recommended lifestyle changes. The participants will also be able to view the comparative report of their clinical parameters (BMI and blood pressure) and the result of the data entered by them (knowledge and lifestyle adherence scores) during every assessment as feedback. Both groups will be followed up after 1, 3, and 6 months to assess their knowledge on prehypertension and adherence to lifestyle practices and record their height, weight, BMI, and blood pressure on-site. At the end of the study, an information booklet on prehypertension will be provided to every college in Udupi District that was included in the study.

#### Study Participants and Sampling

The study will be conducted in the Udupi District of Karnataka, which is divided into 7 taluks (Udupi, Kundapur, Karkala, Hebri, Byndoor, Brahmavar, and Kapu). There are 33 private and 10 government-run colleges in the district. Young adults aged 18-25 years working toward a bachelor of science, bachelor of communication, or bachelor of arts in colleges in Udupi District who meet the inclusion and exclusion criteria (Textbox 1) will be considered for the study.

Inclusion and exclusion criteria for the study.
**Phase 1**
Inclusion criteriaYoung adults aged between 18-25 years studying in selected degree colleges in Udupi District, Karnataka.Young adults willing to participate in the study.Exclusion criteriaYoung adults who have already been diagnosed with hypertension or other systemic disorders.Young adults who are on medications for any other ailments.
**Phase 2**
Inclusion criteriaYoung adults identified to have prehypertension in phase 1.Young adults with prehypertension willing to participate in the study.Young adults with prehypertension having android mobile phones.Colleges with students having prehypertension identified during phase 1 were considered.Exclusion criteriaYoung adults identified to have hypertension in phase 1 and who were already diagnosed with other systemic disorders.Young adults with prehypertension who are on medications for any other ailments.Young adults with prehypertension who do not have android mobile phones.

The calculated sample size for phase 1 was determined to be 381 participants using the following formula for estimating a proportion, where n is the sample size required, Z_1-α/2_ is the desired confidence level (ie, for a 95% confidence level, Z_1-α/2_=1.96), P is the prevalence, and d is the margin of error:

This calculation assumes the prevalence of prehypertension among young adults to be 45% at a 95% confidence level with a 5% margin of error (absolute precision) based on a previous study by Kini et al [7]. After multiplying by a design effect of 2 due to cluster sampling, the sample size was determined to be 762 participants.

The sample size for phase 2 was 34 participants per group, considering a 38% anticipated population SD of the primary outcome variable (ie, the prevalence of prehypertension) obtained using the equation for repeated measures ANOVA given below. In the equation, n is the sample size required, Z_1-α/2_ is the desired confidence level (ie, for a 95% confidence level, Z_1-α/2_=1.96), Z_1-β_ is the power of the test (ie, for a power of 80%, Z_1-β_=0.84), σ² is the population variance (ie, square of the SD), m is the number of groups being compared, ρ is the correlation coefficient between groups, and d is the minimum detectable difference.

Accounting for a 20% dropout rate, the final sample size was 43 participants per group. After multiplying by a design effect of 2 due to cluster randomization, the sample size was determined to be 85 participants per group.

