**Figure 2 figure2:**
[figure not shown]
CONSORT (Consolidated Standards of Reporting Trials of Nonpharmacologic Interventions) 2017 flow diagram for the study. N denotes the number of colleges (ie, clusters) and n denotes the number of participants per cluster. DASH: dietary approach to stop hypertension.

#### Phase 1

After obtaining administrative permission from the Institutional Research Committee, Institutional Ethical Committee, and Joint Director of Collegiate Education, Udupi District, taluks from Udupi District were randomly selected to collect data for assessing the prevalence of prehypertension in phase 1. The data were collected on-site from young adults of colleges from randomly selected taluks. Baseline information, clinical variables, lifestyle practices, knowledge on prehypertension and hypertension, and blood pressure were measured for all participants from the selected colleges. An automated, digital, oscillometric blood pressure machine (Omron) was used to measure blood pressure after device calibration. As of March 29, 2024, phase 1 was completed with data collected from 762 samples from 8 randomly selected colleges.

#### Phase 2

Colleges with students having prehypertension identified during phase 1 were considered as clusters (N=6) and will be allocated to the intervention (N=3) and control groups (N=3) by simple randomization using the chit method. A random allocation sequence using the chit method was generated by research assistants who are not involved in the study. Currently, phase 2 is in progress.

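### The 80% power for phase 2 rests on normal quantiles and a design effect of 2; with 3 colleges per arm, a comparison that respects college randomisation has 4 degrees of freedom and about 56% power on the same inputs

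*Protocol article*

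**What the plan says.** Study Participants and Sampling (Methods) sizes phase 2 in three steps.

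- **Base size.** "The sample size for phase 2 was 34 participants per group", from a repeated measures ANOVA equation with 1.96 for two-sided 5% and "for a power of 80%, Z_1-β_=0.84". The equation's other terms are named, "ρ is the correlation coefficient between groups, and d is the minimum detectable difference", but neither has a stated value.
- **Dropout.** "Accounting for a 20% dropout rate, the final sample size was 43 participants per group".
- **Clustering.** "After multiplying by a design effect of 2 due to cluster randomization, the sample size was determined to be 85 participants per group".

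The Phase 2 paragraph under Study Design fixes the number of clusters. Six colleges "will be allocated to the intervention (N=3) and control groups (N=3) by simple randomization using the chit method".

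The Statistical Analysis section plans a repeated measures ANOVA over four time points, on a per protocol basis. It does not mention college.

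**The concern.** A design effect corrects the variance of the arm difference for similarity among students of the same college. It does not correct the reference distribution. When whole colleges are randomised, the error of the arm comparison has to be estimated from variation between colleges. Six colleges in two arms leave 4 degrees of freedom for that. Normal quantiles are a fair approximation with many clusters, but not with six.

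Two things are at stake, depending on the analysis finally used.

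- If the analysis respects college, the trial has much less power than stated, and a non-significant result could be over-read as evidence that the app does not work.
- If the analysis ignores college, the risk runs the other way, towards a false positive.

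The sample size section warns of neither.

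**Working it through.** **Inputs, all from the protocol article.** Quantiles 1.96 and 0.84; base size 34 per group; dropout 20%; design effect 2; 3 colleges per arm.

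**1. Reproduce the plan's figures.**
- 34 / 0.8 = 42.5, rounded to 43.
- 42.5 × 2 = 85 per group (43 × 2 = 86 if rounded first).
- The noncentrality implied by the quantiles is 1.96 + 0.84 = 2.80. Power with a normal reference is Φ(2.80 − 1.96) = Φ(0.84) = 80.0%.

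The chain holds on its own terms. The starting value of 34 cannot be rebuilt, because d and ρ have no stated values. The power check does not need them, since the two quantiles fix the noncentrality.

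**2. Same inputs, college-level reference distribution.**
- Completers per arm: 85 × 0.8 = 68. Effective size: 68 / 2 = 34, so the noncentrality stays at 2.80.
- Degrees of freedom: 2 × 3 − 2 = 4. Critical value: t(0.975, 4) = 2.776.
- Power = P(|T| > 2.776), with T noncentral t on 4 degrees of freedom and noncentrality 2.80, = 56.4%.
- A simulation of a t-test on college means, 3 against 3 (200,000 runs), gave 56.5%.

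**3. What 80% power would need.** On 4 degrees of freedom the noncentrality must be 3.76. The ratio 3.76 / 2.80 = 1.34 is the factor on the detectable difference; its square, 1.80, is the factor on information.

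**4. Sensitivity to the design effect (68 completers per arm).** Noncentrality = 2.80 × √(2 / design effect).

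| Design effect | Noncentrality | Power, 4 df |
|---|---|---|
| 1.5 | 3.23 | 68% |
| 2 | 2.80 | 56% |
| 3 | 2.29 | 42% |

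**5. Sensitivity to dropout (85 per arm retained).** Noncentrality = 2.80 × √(effective size / 34).
- Design effect still 2: effective size 85 / 2 = 42.5, noncentrality 3.13, power 65%.
- Intracluster correlation held instead at the value that gives a design effect of 2 among completers: 1 / (68/3 − 1) = 0.046. The design effect becomes 1 + (85/3 − 1) × 0.046 = 2.26, the effective size 37.6, the noncentrality 2.94 and the power 60%.

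**6. Would more students help?** Little. At a correlation of 0.046, even 200 completers in each of three colleges per arm give only 78%. At about 22.7 completers per college, four colleges per arm would give 77% and five 88%. The shortfall comes from the number of colleges.

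**7. If the ANOVA ignored college.** At a true design effect of 2, the real standard error is √2 times the one used. The two-sided type I error is 2 × [1 − Φ(1.96 / √2)] = 2 × [1 − Φ(1.386)] = 16.6%. The rejection rate at the planned difference would be about 92%, but from a test that does not hold its level.

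**The case against.** **The 56% belongs to a test the article does not describe.** This is partly right. The article plans a repeated measures ANOVA and does not say how college enters it. A reader might infer that college will be ignored and that false positives are therefore the main problem. The article is silent rather than explicit, and a fuller analysis plan may exist, so that reading is not established. The power claim fails either way: with college respected, power is about 56%; with college ignored, the nominal power comes with a type I error of about 17%.

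**The figure is conditional.** This stands. It assumes the full 20% dropout, a design effect of exactly 2 and a single unadjusted arm contrast. Other values give 42–68% across design effects of 3 to 1.5, and 60–65% with no dropout. A group-by-time test could have different degrees of freedom, and covariate adjustment could recover some precision, but the article describes none.

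**The detectable difference in SD units.** It is tempting to convert 34 effective participants per group into a standardised difference with the two-sample formula. The documents do not support this. The 34 came from a repeated measures equation whose d and ρ are not given, so only the ratio of 1.34 can be stated. The planned difference itself is also undefined: the sample size text ties its 38% SD to the prevalence of prehypertension, while the Outcomes section names blood pressure.

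**It is late.** The progress table shows baseline to 3 months completed and the 6-month visits under way. That rules out adding colleges as a realistic remedy. It does not stop the power statement and the analysis from being corrected.

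**Conclusion.** The point holds in conditional form. The sample size arithmetic is reproducible, so this is not a calculation slip. The fault is a method that takes no account of having only six clusters. On the protocol's own inputs, a comparison that respects college randomisation has about 56% power rather than 80%, so the type II risk at the planned difference is about 44% rather than 20%. Power stays below 80% at every design effect and dropout rate examined above, and 80% applies only to a difference about 1.34 times the planned one.

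A reader should not take 56% as a fixed property of the trial, nor as the power for any particular fall in blood pressure. It rests on a true design effect of 2, 20% dropout, one unadjusted arm contrast on 4 degrees of freedom, and the unstated difference behind the 34 per group.

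**What to change.** Keep six colleges and 85 per group, and make three changes.

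1. **Study Participants and Sampling.** Restate the power, for example: *about 56% (roughly 42–68% for design effects of 3 to 1.5) for a college-level comparison on 4 degrees of freedom; 80% power applies to a difference about 1.34 times as large.* State the dropout assumption with it.
2. **Statistical Analysis.** Say that the primary arm comparison accounts for college with 4 degrees of freedom. A t-test on college-level mean change would do, or a mixed model with a college random effect and small-sample degrees of freedom. Report the result as an estimate with a 4-df confidence interval. Without this change the protocol would quote power for one test and plan another.
3. **Design effect.** Check the value of 2 against the intracluster correlation from the phase 1 data (762 students in 8 colleges), and revise the power range if it differs.

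The cost is some redrafting, a less favourable stated power and a wider confidence interval. No new data are needed.

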### Outcomes

The primary outcome is blood pressure, and the secondary outcomes are adherence to lifestyle practices and knowledge on prehypertension and hypertension.

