**Methods:**

The study consists of 2 phases. Phase 1 used a cross-sectional survey design, and phase 2 included a pragmatic randomized controlled trial with cluster randomization. The protocol was prepared according to the SPIRIT (Standard Protocol Items: Recommendations for Interventional Trials) 2013 checklist. The CONSORT (Consolidated Standards of Reporting Trials of Nonpharmacologic Interventions) 2017 guideline was followed for reporting the protocol. The estimated sample size for phase 1 was 762 participants, and the sample size for the phase 2 was 85 participants per group. Both the control and experimental groups will receive education on prehypertension and hypertension, with the experimental group additionally receiving an mHealth app. The experimental group’s adherence to lifestyle practices will be monitored every 15 days, and reminder messages will be sent to nonresponders. Both groups will be followed up with on-site after 1, 3, and 6 months to assess their knowledge on prehypertension and hypertension, blood pressure, and lifestyle practices. The primary outcome of the study will be an improvement in blood pressure readings. The secondary outcomes will include adherence to lifestyle practices and knowledge on prehypertension and hypertension.

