## Introduction

Hypertension is the third most significant risk factor contributing to the burden of noncommunicable diseases (NCDs) and places a considerable public health burden on cardiovascular health in India [1]. According to the World Health Organization, hypertension is a leading cause of premature death, with prehypertension serving as a critical precursor to hypertension both nationally and globally [2]. The seventh report of the Joint National Committee classifies prehypertension as a systolic blood pressure of 120-139 mmHg or a diastolic blood pressure of 80-89 mmHg [3]. However, the eighth report of the Joint National Committee guidelines do not define prehypertension because their recommendations focus on individuals with diagnosed hypertension [4]. Despite the rising prevalence, increased awareness, and availability of treatments, hypertension remains poorly controlled, particularly in low-income and middle-income countries, leading to major cardiovascular events [2].

A study conducted in India revealed that the prevalence of hypertension and prehypertension among young adults is 11.2% and 33.3%, respectively [5]. Individuals with a family history of hypertension and those who are physically inactive have a higher risk of hypertension [6]. Identifying prehypertension during its asymptomatic stage allows for timely interventions to normalize blood pressure, thereby preventing or delaying the onset of hypertension [7].

Many young adults with increased blood pressure remain undiagnosed, and a substantial proportion of individuals are unaware of their existing prehypertension. Young people are one of India’s most valuable resources. Studies in India reported the prevalence of prehypertension among young adults to be in the range 24.6%-65% [5,7-13].

Mobile devices have become integral to health care, providing easy access to health information both at home and on the go [14]. Early identification of prehypertension enables proactive blood pressure management through preventive strategies, thereby reducing cardiovascular morbidity and mortality.

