### Statistical Analysis

Data analysis will be conducted using jamovi (version 2.3.21; The jamovi project), using both descriptive and inferential statistics in line with the study objectives. For descriptive statistics, means and SDs will be used because all study outcomes are quantitative and continuous. Because the study involves assessing outcomes at 4 time points (baseline, 1 month, 3 months, and 6 months), repeated measures ANOVA will be used to evaluate the effectiveness of the intervention, and per protocol analysis will be used.

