## Discussion

### Study Overview

The primary objective of the study is to enhance awareness on prehypertension and hypertension among young adults, the productive population of the country, thereby promoting positive health and preventing premature CVDs. Globally, hypertension is responsible for 10.4 million deaths annually [15]. Prehypertension, an early stage of hypertension, can be effectively managed with proactive measures, thereby delaying or preventing the future risk of hypertension and its complications [16].

Evidence from a study conducted in Southern India suggests a 45.2% prevalence of prehypertension among young adults (aged 20-30 years). The study also revealed that prehypertension risk is associated with obesity and several lifestyle factors, including unhealthy dietary habits and occupation-related physical inactivity [7]. Although hypertension was once considered a disease of adults, studies now show an alarming rise in cases among younger age groups [2].

CVD accounts for approximately 17.9 million deaths globally among middle-aged adults, with 20%-50% of these deaths attributed to hypertension-related cardiovascular conditions [2]. In India, hypertension is highly prevalent, affecting 1 in 3 adults. With an estimated 762 million people aged 18 years or older in India, this translates to 234 million adults living with hypertension. The rising prevalence of hypertension, particularly among young adults, poses a significant socioeconomic burden if not addressed promptly [9,18]. Globally, the number of adults with hypertension, estimated at 1 billion in 2000, is expected to double to 2 billion by 2025 [33]. Research strongly supports the role of lifestyle interventions as an essential measure in effective blood pressure control and the reduction of CVD-related morbidity and mortality [9,17,20].

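### Phase 2 is sized on the prevalence of prehypertension although blood pressure is the declared primary outcome, and no component or contrast of blood pressure is fixed as decisive

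*Protocol article*

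**What the plan says.** - **Declared primary outcome.** The Outcomes section says "The primary outcome is blood pressure, and the secondary outcomes are adherence to lifestyle practices and knowledge on prehypertension and hypertension". The Abstract (Methods) agrees: "The primary outcome of the study will be an improvement in blood pressure readings". Neither names systolic or diastolic pressure, a visit, or a contrast.
- **Variable behind the sample size.** Under Study Participants and Sampling, the phase 2 figure of 34 per group rests on "considering a 38% anticipated population SD of the primary outcome variable (ie, the prevalence of prehypertension". It is raised to 43 for 20% dropout and to 85 with a design effect of 2, at 80% power and two-sided 5%.
- **Entry to phase 2.** The inclusion criteria admit only people classified as prehypertensive in phase 1.
- **Analysis.** The Statistical Analysis section says "means and SDs will be used because all study outcomes are quantitative and continuous" and plans a repeated measures ANOVA over baseline and three follow-up visits. It does not say whether the group, time or group-by-time effect decides.
- **Components and visits.** The Introduction defines prehypertension by a "systolic blood pressure of 120-139 mmHg or a diastolic blood pressure of 80-89 mmHg". The Abstract adds "Both groups will be followed up with on-site after 1, 3, and 6 months".
- **Discussion.** The Study Overview opens with "The primary objective of the study is to enhance awareness on prehypertension and hypertension among young adults", whereas the Outcomes section lists knowledge as secondary.

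**The concern.** A sample size supports a trial's main claim only if it was computed for the variable that carries the claim. Here it was computed for another one. If blood pressure is primary, as two sections say, the reader does not know what difference in mmHg the trial can detect, and a null result could not be read as evidence against a stated effect. If prevalence is primary, the Outcomes section is wrong, and so is the statement that every outcome is continuous.

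A second, lesser gap follows. Blood pressure is two measurements, and the planned ANOVA yields several effects. Unless one is designated, the result reported as primary can be chosen after the data are seen. A time effect, for example, could be read as improvement even if both arms improve equally, since both receive the education session.

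**Working it through.** **1. Reproduce the plan's figures.** Inputs from the phase 2 sample size paragraph: 34 per group, 20% dropout, design effect 2.
- 34 / (1 − 0.20) = 42.5, rounded up to 43.
- 42.5 × 2 = 85 (or 43 × 2 = 86 if rounded first).

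The inflation steps hold within rounding.

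**2. What the base figure of 34 was computed for.** The paragraph defines d, m and ρ but gives no values for them, so 34 cannot be reproduced. The displayed equation is not legible in the available text, so I assume the common form n = 2(1.96 + 0.84)²σ²[1 + (m − 1)ρ] / (m d²). Solving for d with n = 34 and σ = 38:
- m = 1: d = √(2 × 7.84 × 1444 / 34) = √665.9 = 25.8 percentage points.
- m = 4, ρ = 0: d = √(665.9 / 4) = 12.9 percentage points.
- Over the assumed ranges m = 1-4 and ρ = 0-0.8, d runs from about 13 to 26 percentage points, or 0.34 to 0.68 SD.

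None of this converts to mmHg, because the article gives no blood pressure SD.

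**3. Whether 38% fits prevalence.** A yes/no variable with proportion p has SD √[p(1 − p)].
- At the 45% used for phase 1: √(0.45 × 0.55) = 0.50.
- An SD of 0.38 needs p(1 − p) = 0.1444, so p is about 17.5% or 82.5%.
- By the phase 1 classification that governs entry, p is 100% in both arms, where the SD is 0.

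So 38% matches neither the 45% nor the entry value, and its origin cannot be traced.

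**4. Cost of leaving the component open.** Two-sided 5% tests, no true effect, normal test statistics.
- One ANOVA-based test per component, independent: 1 − 0.95² = 9.75%.
- The same at an assumed correlation of 0.7 between components: 8.4% (400,000 simulated draws).
- Counting only results that favour the app: at most 1 − 0.975² = 4.9%.
- Upper bound, six separate tests (2 components × 3 visits): 16-23%, with assumed correlations of 0.4-0.7 between components and 0.4-0.8 between visits. Counting only results that favour the app, 8-12%.

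These rates ignore clustering, which is a separate matter.

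**5. Price of keeping both components.** With 0.025 for each, the required size rises by (2.241 + 0.842)² / (1.960 + 0.842)² = 9.505 / 7.851 = 1.21, so 85 × 1.21 is about 103 per group. If enrolment stays as it is, a design with 80% power at 5% has Φ(2.802 − 2.241) = Φ(0.561), or about 71%, per component.

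**The case against.** **The two variables are related.** Prehypertension is defined from blood pressure, so a fall in pressure lowers the proportion affected. A standardised difference is also scale-free, so 85 per group might happen to suit a mean difference. That is possible, but it would be coincidence. Without an SD and a target in mmHg, nothing in the article shows it.

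**This is a condensed article.** A fuller protocol or analysis plan may name the component and the contrast. This stands in part: that gap is an omission, not a contradiction, and deserves less confidence. It does not help the sample size paragraph, because no later document can make that paragraph and the Outcomes section both right about which variable is primary.

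**A reader might infer three competing primary outcomes, with success claimable on any of them, including knowledge.** The article does not support that. The Discussion sentence states a broad aim of the whole study and sets no outcome, test or success rule. The Abstract and the Outcomes section both make knowledge secondary, and the title concerns blood pressure. It is loose wording that should be aligned.

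**A reader might also take the six-test figure as the trial's error rate.** The article plans a repeated measures ANOVA, which can test the visits together, and nowhere plans a 5% test at each visit. Six tests is an upper bound only.

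**Conclusion.** The contradiction over the primary variable is real and nothing in the article resolves it. The 80% power and the 85 per group are attached to prevalence with a 38% SD, not to blood pressure. How far power for blood pressure departs from 80% cannot be stated, in either direction, because no mmHg inputs are given.

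The unspecified component is a smaller matter: about 8-10% instead of 5%, two-sided, if each component gets its own 5% test. This rests on an assumed correlation between 0.7 and 0 and on no other document fixing the choice.

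This should be corrected before outcomes are compared by arm. It affects how the primary result can be interpreted, not the conduct of the trial.

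**What to change.** 1. **Name one primary variable and one contrast** in a dated record made before outcome data are compared by arm. Examples are the between-arm difference in systolic pressure at 6 months adjusted for baseline, the group-by-time effect for one component, or both components with a stated alpha split. Which is chosen matters less than fixing one.
2. **List the rest as secondary:** the other component, the other visits, the proportion prehypertensive, adherence and knowledge.
3. **Repair the sample size paragraph.** Restate the calculation for the chosen variable in mmHg with SD, d, m and ρ. Otherwise, state plainly that 85 per group was derived for prevalence and that power for blood pressure is not established. Deleting the word prevalence would not do, because the 38% SD belongs to that variable and the mismatch would only be hidden.
4. **Align the other sections.** Bring the Discussion sentence on awareness and the statement that all outcomes are continuous into line with the choice.

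Timing matters. The Results section expects 6-month assessments to finish by June 30, 2025, and the article is dated August 7, 2025, so data collection may already be over. The record should say so and confirm that no comparison by arm had been seen.

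The cost is a short amendment and one recalculation or disclosure, with enrolment unchanged. The price is less freedom to highlight other outcomes, and a power statement that may be less favourable or remain unproven.
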